#### *Safety*

Adverse events (AEs) and adverse drug reactions (ADRs) will be monitored and reported throughout the study. The incidence of AEs and ADRs will be compared between groups using the *χ*^2^ test with the level of significance set at *P* < 0.05.

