**Methods:**

In this multicenter, randomized, controlled, double-blind, double-dummy clinical trial, in which we will use the comparative effectiveness research method, we will compare the efficacy of two commonly used Chinese patent medicines for angina patients diagnosed with qi deficiency and blood stasis syndrome. A total of 160 patients will be recruited and randomly assigned to receive either (1) QiShenYiQi dripping pills, Tongxinluo placebo and routine medication or (2) Tongxinluo capsules, QiShenYiQi placebo and routine medication. These treatment regimens will be carried out for 4 weeks, followed by a 10-day washout period and a 4-week crossover phase in which the treatments in the two patient groups will be exchanged. Patients will be allowed to choose symptoms that matter most to them and will be grouped accordingly. Patient-reported outcomes such as the Seattle Angina Questionnaire score and the 15-point Likert scale score will be measured and reported. The minimally clinical important difference will be calculated and used for efficacy assessment, and correspondence analysis will be performed to identify the best indications for each drug.

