## Methods

### Study design

We will conduct a multicenter, randomized, crossover, double-blind, double-dummy clinical trial. A flowchart of the study protocol is shown in Figure 1.

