### Sample size calculation

Sample size estimation is based on the results of a pilot study that showed the difference in changes in Seattle Angina Questionnaire (SAQ) scores of 2 ± 2.5 between the group receiving QSYQ dripping pills and the group taking TXL capsules. Assuming a two-sided *P*-value of 0.05, 90% power and calculating for a dropout rate of 20%, one would need to have approximately 160 patients with 80 in each treatment group. We used the PAST software program to calculate these statistics (http://folk.uio.no/ohammer/past/) [10]. Therefore, we plan to recruit 40 patients for each of the four symptom combinations, from among whom 20 will be assigned to treatment arm A (QSYQ) and 20 to treatment arm B (TXL). In all, 160 patients will be recruited.

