#### *Assignment of interventions*

In this study, we adopt a crossover design which involves three key phases: a 4-week treatment period, a 10-day washout period and the crossover of treatment for another 4 weeks:

1. The first treatment period (4 weeks): A total of 160 participants will be randomly assigned to receive treatment A or treatment B for 4 weeks.

1.a. Treatment A: QSYQ dripping pills + TXL placebo + routine medication

1.b. Treatment B: TXL capsules + QSYQ placebo + routine medication

2. Washout phase (10 days): After the first round of treatment, patients in both groups will receive QSYQ placebo and TXL placebo plus routine medication for 10 days.

3. Crossover of treatments (4 weeks): In this stage, patients formerly assigned to treatment A will be switched to treatment B and those assigned to treatment B will be switched to treatment A.

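### The adverse-event comparison uses a chi-square test for independent groups in a crossover: read by randomised sequence it does not compare the two drugs, and read by drug received it ignores the pairing

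*Protocol article*

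**What the plan says.** The Study design section fixes the design: "We will conduct a multicenter, randomized, crossover, double-blind, double-dummy clinical trial". Under Assignment of interventions, after four weeks of treatment and a placebo washout, "patients formerly assigned to treatment A will be switched to treatment B and those assigned to treatment B will be switched to treatment A". Every patient who completes the trial therefore takes both QSYQ (treatment A) and TXL (treatment B).

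Under Safety, adverse events (AEs) and adverse drug reactions (ADRs) "will be monitored and reported throughout the study". The analysis follows in one sentence: "The incidence of AEs and ADRs will be compared between groups using the" chi-square "test with the level of significance set at *P* < 0.05". The section does not define the groups, does not assign events to a period or a drug, and does not mention that each patient contributes under both drugs.

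Elsewhere, when the article speaks of the groups in this crossover, it means the two randomised groups. The abstract describes "a 4-week crossover phase in which the treatments in the two patient groups will be exchanged", and the washout text says that "patients in both groups will receive QSYQ placebo and TXL placebo plus routine medication for 10 days". The sample size section plans "approximately 160 patients with 80 in each treatment group".

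**The concern.** The usual chi-square test for two groups assumes that different people stand on the two sides and that the sides differ in the treatment taken. In this crossover, a comparison over the whole study cannot meet both conditions among completers. Split by sequence, the sides are different people, but both have had both drugs. Split by drug received, the sides differ in drug but are the same people.

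Under the first split, a non-significant result could be reported as showing no safety difference between the drugs, although the test could not have found one. Under the second, the nominal 5% level does not hold.

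**Working it through.** The article gives no AE rate and no power for safety, so there is no stated figure to reproduce. From the documents: 160 patients, 80 per sequence, two periods, two-sided 5% level, 20% dropout allowance. The AE rates and within-patient correlations below are assumptions, shown over a range.

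**1. Groups as sequences, events over the whole study.** Let pA and pB be the per-period AE risks. With no order or carry-over effect, and with independent periods for simplicity, the chance of at least one AE is 1 − (1 − pA)(1 − pB). The formula is symmetric in A and B, so it is the same for both sequences. For 5% and 20% it is 1 − 0.95 × 0.80 = 24% in A-then-B and 24% in B-then-A. The expected difference is zero, although one drug has four times the risk of the other.

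**2. Groups as drug received, both periods pooled.** With n patients and AE indicators correlated by φ within patient, under equal risk p:
- variance assumed by the chi-square test: 2p(1 − p)/n
- actual variance of the difference: 2p(1 − p)(1 − φ)/n

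For φ > 0 the test overstates the variance, so its actual size is below 5%.

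**3. Simulation.** 20,000 trials per row, 80 per sequence, everyone completing, no period or carry-over effect, Pearson chi-square without continuity correction, asymptotic McNemar. The correlation is on a latent normal scale. Entries are rejection rates.

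| AE risk per period, A vs B | Correlation | By sequence, whole study | By drug, pooled | Period 1 only | McNemar |
|---|---|---|---|---|---|
| 10% vs 10% | 0 | 0.048 | 0.050 | 0.048 | 0.051 |
| 10% vs 10% | 0.3 | 0.049 | 0.034 | 0.049 | 0.050 |
| 10% vs 10% | 0.6 | 0.049 | 0.020 | 0.050 | 0.054 |
| 5% vs 15% | 0 | 0.050 | 0.871 | 0.572 | 0.872 |
| 5% vs 15% | 0.3 | 0.050 | 0.881 | 0.571 | 0.907 |
| 5% vs 15% | 0.6 | 0.049 | 0.907 | 0.567 | 0.958 |
| 5% vs 20% | 0.3 | 0.051 | 0.993 | 0.847 | 0.995 |
| 10% vs 30% | 0.3 | 0.047 | 0.998 | 0.904 | 0.999 |

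The sequence column stays at the significance level in every row.

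**4. Stronger clustering within patients.** A second model uses a patient effect on the logit scale, a typical patient's risk of 10% per period and, for power, a drug log-odds ratio of 1.

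| Logit SD | Latent correlation | Pooled chi-square: size | Pooled chi-square: power | Exact McNemar: power |
|---|---|---|---|---|
| 1 | 1/(1 + π²/3) = 0.23 | 0.039 | 0.878 | 0.876 |
| 2 | 4/(4 + π²/3) = 0.55 | 0.015 | 0.744 | 0.837 |
| 3 | 9/(9 + π²/3) = 0.73 | 0.005 | 0.498 | 0.748 |

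Exact McNemar is itself conservative (size about 0.03), which is why it gains nothing at SD 1.

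**5. Dropout.** Suppose all of the planned 20% leave after period 1, unrelated to AEs. For 5% vs 15%, the chance of any AE in a completer is 1 − 0.95 × 0.85 = 0.1925. The expected incidences are
- A-then-B: 0.8 × 0.1925 + 0.2 × 0.05 = 0.164
- B-then-A: 0.8 × 0.1925 + 0.2 × 0.15 = 0.184

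The difference is 0.2 × (0.15 − 0.05) = 0.02, one fifth of the true 0.10. With mean incidence 0.174, the standardised difference is 0.02/√(2 × 0.174 × 0.826/80) = 0.33, which gives power of about 6%. Dropout makes the contrast not exactly null, but hardly informative.

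**The case against.** The strongest reply is that the Safety section never defines its groups, so it cannot be said flatly that the test fails to compare the drugs. That stands. A reader might infer from the crossover that QSYQ and TXL are never compared for safety; the text does not support so firm a statement. The sample size section also labels the arms by drug and, in describing the pilot study, speaks of groups by the drug taken. On a drug-received reading the drugs are compared, and the error is on the conservative side. At low correlation the power loss is negligible.

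A second reply is that the phrase about the whole study belongs to the sentence on monitoring, and that efficacy is assessed period by period. A chi-square test within each period would set QSYQ against TXL in different patients and would be valid. This also stands as a possibility, but the section does not state it. A period-1-only version would discard half the data: power is about 0.57 at 5% vs 15%, against 0.87 to 0.96 within patients.

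A third reply is that event attribution and paired intervals are matters for the analysis plan, in a study that calls itself exploratory and whose stated objectives concern effectiveness and methodology. That limits the weight of the point but does not remove it: the article itself names the comparison, the test and the significance level, and these do not fit its own design.

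**Conclusion.** The point holds in conditional form. On the article's usual sense of groups, with AEs counted over the whole study, the stated test has power equal to its 5% level for any QSYQ–TXL difference, apart from order, carry-over and dropout effects. The exact zero difference applies only to patients who complete both periods.

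On the drug-received reading the test answers the right question with the wrong variance. Its actual size is about 2% to 4% at moderate correlation and 0.5% to 1.5% at an assumed logit SD of 2 to 3. The power loss is material only in that last range, and nothing in the article indicates that correlation is so high. A reader might infer that the paired structure invalidates the drug-received test in every case, or inflates false positives; with positive correlation it does neither.

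The sentence should be corrected. The consequence is confined to safety. All AE rates and correlations used here are assumptions.

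**What to change.** Replace the comparison sentence with text that does the following:

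- attributes each AE or ADR to the treatment of the period in which it starts, with a prespecified rule for onsets during the washout;
- compares QSYQ with TXL within patients who have both periods, using the Mainland-Gart test (which allows for a period effect) or an asymptotic or mid-P McNemar test, and reports the paired risk difference with a 95% confidence interval;
- tabulates AEs and ADRs by drug received for all treated patients, so that those who leave in period 1 are not lost from the safety account.

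An exact McNemar test is not the best choice here because it is conservative itself. If the sponsor did intend a comparison within periods, the text should say so and accept the lower power.

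The cost is a few sentences and a little more analysis work. It needs AE onset dates but no new visits, and it leaves efficacy untouched.

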#### *Drug management*

The central drug administrator will be responsible for drug distribution to and reclamation from each center. Drug administrators at each center will hand out test drugs to the patients and reclaim unused drugs. A drug management log book will be kept.

#### *Data management*

Oracle Clinical Version 4.6 software (Oracle, Redwood Shores, CA, USA) will be used for clinical data management.

## Discussion

TCM syndrome differentiation is the key to understanding the condition or disease and also to choosing the best means of treatment according to traditional Chinese beliefs. It is also held that the efficacy of TCM is most obviously observed in alleviating or improving the characteristic symptoms of patients diagnosed with the corresponding TCM syndrome.

We will conduct a multicenter, randomized, double-blind, double-dummy trial to compare the effectiveness of two Chinese patent drugs, namely, QSYQ and TXL, for angina patients with qi deficiency and blood stasis syndrome.

The study features the grouping of patients with varied treatment needs, the integration of PIO and PRO in efficacy assessment and the use of CA in identifying the most significant correlations between different symptom combinations and treatment outcomes. The ultimate goal of this exploratory study is to establish a methodology for the precise identification of the characteristic indications for which a Chinese patent drug is most effective, and thus differentiation from other drugs used for similar clinical indications in clinical use.

### Strengths and limitations

#### *Strengths*

The following are the potential strengths of our study protocol:

1. Evaluation and interpretation of the therapeutic effects of Chinese patent medicine from the patient’s own perspective

2. Highlighting of individualized evaluation of Chinese patent medicine.

3. Analysis of the curative effects of Chinese patent medicine on single- or multiple-symptom combinations

4. Visualized display of the correspondence between the drug’s efficacy and a specific indication or group of indications

5. Comparison of the therapeutic effects of Chinese patent drugs with other drugs used for similar clinical

#### *Limitations*

The proposed methodology needs to be tested for practicality and feasibility in practice.

#### *Implications*

By comparing the effects of two kinds of Chinese patent medicine on angina symptom improvement, we aim to establish an innovative evaluation methodology that can facilitate the widespread and rational use of Chinese patent drugs by practitioners of TCM and Western medicine.
